### Study design, treatments, and blinding

The ISTRA ADJUST PD study is a multicenter, randomized, open-label, parallel-group controlled study (Fig. 1). Study participants will be randomly assigned to either the istradefylline group or the control group in a 1:1 ratio. Randomization will be centrally performed via computer allocation, using a minimization method and stratified according to age (< 60 or ≥ 60 years), levodopa equivalent dose (< 400 or ≥ 400 mg/day), and dyskinesia (presence or absence). The study will be conducted from February 2019 to February 2022 (with the registration period lasting until November 2020), and the expected duration of involvement for each participant is 37 weeks. The observation schedule is shown in Table 1; most observations will be conducted at 4- or 12-weekly intervals during the study period.

**Fig. 1 Fig1:**
[figure not shown]
ISTRA ADJUST PD study design. W, week

**Table 1 Tab1:** Observation schedule

	Date of consent or enrollment	Observation period (week)											
		0	1^a^	4	8	12	16	20	24	28	32	36^b^	37^c^
Informed consent	●												
Eligibility confirmation	●	●											
MMSE	●												
Patient background	●												
Medical history/complications		●											
Decision on dose increase of levodopa-containing medications				●	●	●	●	●	●	●	●	●	
CGI-S		●		●	●	●	●	●	●	●	●	●	
CGI-I				●	●	●	●	●	●	●	●	●	
PGI-S		●		●	●	●	●	●	●	●	●	●	
PGI-I				●	●	●	●	●	●	●	●	●	
mH&Y (ON/OFF)		●				●			●			●	
MDS-UPDRS (part I, II, III, IV)		●				●			●			●	
PDQ-39		●				●			●			●	
Wearable device data	●					●			●			●^e^	
Symptom diary^d^	●					●			●			●^e^	
Hospitalizations	●	●	●	●	●	●	●	●	●	●	●	●	●
Concomitant medication check	●	●	●	●	●	●	●	●	●	●	●	●	●
Adverse events	●	●	●	●	●	●	●	●	●	●	●	●	●
Information on discontinuation		At any time											
Data entry into the case report form		Within 2 weeks after each visit											

*CGI-I* clinical global impressions of improvement, *CGI-S* clinical global impressions of severity, *MDS-UPDRS* Movement Disorder Society Unified Parkinson’s Disease Rating Scale, *mH&Y* modified Hoehn & Yahr scale, *MMSE* Mini-Mental State Examination, *PDQ* Parkinson’s disease questionnaire, *PGI-I *patient global impressions of improvement, *PGI-S* patient global impressions of severity

^a^Istradefylline group only

^b^Or the day immediately after discontinuation

^c^Not a mandated visit if judged to be unnecessary

^d^Symptoms will be recorded in symptom diaries by study participants or their family members/caregivers. The investigator, subinvestigator, or study cooperator are also allowed to record symptoms in the diary during the visit, or in the case that the patients are hospitalized. Visits will be conducted in an outpatient setting; however, inpatient visits will also be allowed if needed

^e^Wearable devices will be worn for one additional week after the end of the observation period (from Week 36), and symptoms are also recorded in the diary during this period; if the patient has discontinued, these recordings are terminated on the day of discontinuation

The criteria for the titration of levodopa-containing medications are as follows: if the clinical global impression of severity scale (CGI-S) is ≥ 4 on the day of observation, the dose is incrementally increased by 50 mg/day. If an intolerable adverse reaction occurs due to the dose increase, reduction of the dose of the levodopa-containing medication is allowed (at the physician’s discretion; no reduction amount is specified). For levodopa, only a dose increase of 50 mg/day per visit will be allowed.

Once-daily oral administration of a 20 mg istradefylline tablet will be started at Week 0. At Week 1, if the treatment is well tolerated and motor symptoms persist, the dosage of istradefylline will be increased to 40 mg, once daily. Dose reduction is allowed if treatment is not tolerable.

Changes in the dosage and dosing regimen of anti-PD drugs are not permitted within 4 weeks before enrollment and during the treatment period. However, dose reduction of a specific drug is permitted, if intolerable adverse reactions causally associated with that drug appear.

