**Methods:**

This 37-week, multicenter, randomized, open-label, parallel-group controlled study in PD patients aged 30–84 years who are experiencing the wearing-off phenomenon despite receiving levodopa-containing medications ≥ 3 times daily (daily dose 300–400 mg) began in February 2019 and will continue until February 2022. Enrollment is planned to attain 100 evaluable patients for the efficacy analyses. Patients will receive adjunctive istradefylline (20 mg/day, increasing to 40 mg/day) or the control in a 1:1 ratio, stratified by age, levodopa equivalent dose, and presence/absence of dyskinesia. During the study, the levodopa dose will be increased according to symptom severity. The primary study endpoint is the comparison of the cumulative additional dose of levodopa-containing medications during the treatment period between the adjunctive istradefylline and control groups. Secondary endpoints include changes in efficacy rating scales and safety outcomes.

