### Efficacy outcomes

The primary study endpoint is the comparison of the cumulative additional dose of levodopa-containing medications during the treatment period (from Week 0 to Week 37) between patients with PD who receive adjunctive istradefylline and those who do not.

Secondary efficacy endpoints are the between-group comparisons of additional levodopa doses on each observation day from Week 4 to Week 36; the number of days until the first dose increase after Week 4; change in dose of levodopa-containing medications until Week 36; CGI-S score and change in score; CGI-improvement scale (CGI-I) score (to measure the degree of improvement from the previous evaluation); patient global impression of severity (PGI-S) score and change in score; PGI-improvement (PGI-I) score (to measure the degree of improvement from the previous evaluation); mH&Y staging scale (ON/OFF) score and change in score; MDS-UPDRS part I score (nonmotor experiences of daily living), part II score (motor experiences of daily living), part III score (motor examination), part IV score (motor complications), and change in scores; Parkinson’s Disease Questionnaire-39 (PDQ-39) score and change in score; and correlations between any of the score changes. Correlations between CGI-S and other measures (e.g., MDS-UPDRS3, MDS-UPDRS4, and PGI-S) will be evaluated to confirm whether dose escalation decisions would differ between using CGI-S and using other measures.

Patients will also wear a wristband-type triaxial accelerometry system (UW-301BT, Hitachi Systems Ltd., Tokyo, Japan) on their non-dominant wrist for 7 days every 3 months during the study; data extracted from the wearable device will include movement frequency and intensity, gait (step count, pace, and laterality), and sleep (bedtime, awakening time, duration of sleep, sleep efficiency, sleep onset latency, movement during sleep, and number of episodes of getting out of bed).

Safety endpoints for this study will include adverse events and adverse drug reactions classified based on System Organ Class and Preferred Term defined in the Medical Dictionary for Regulatory Activities (Japan edition), using the most recent version at the time of coding.

Exploratory endpoints include evaluation of the correlation between the information extracted from the wearable device and the primary/secondary efficacy endpoints.

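### Adverse events, hospitalisations and concomitant drugs are collected at Week 1 in the istradefylline arm only, so early safety ascertainment differs by arm

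*Protocol article*

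**What the plan says.** Table 1 gives three rows a mark at Week 1: hospitalisations, "Concomitant medication check" and adverse events. No other row is marked there. Footnote a to the Week 1 column reads "Istradefylline group only". Both arms then share the visits at Weeks 4, 8, 12 and so on to Week 36. The same three rows are the only collection items marked at Week 37, where footnote c says "Not a mandated visit if judged to be unnecessary".

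The section on study design, treatments and blinding gives the reason for the Week 1 visit: "At Week 1, if the treatment is well tolerated and motor symptoms persist, the dosage of istradefylline will be increased". It also states the design: "The ISTRA ADJUST PD study is a multicenter, randomized, open-label, parallel-group controlled study", with patients assigned to "either the istradefylline group or the control group in a 1:1 ratio".

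Under Efficacy outcomes, "Safety endpoints for this study will include adverse events and adverse drug reactions classified based on System Organ Class and Preferred Term". The abstract places safety among the secondary endpoints: "Secondary endpoints include changes in efficacy rating scales and safety outcomes".

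**The concern.** A randomised comparison of adverse events needs both arms to be asked the same questions at the same times. Here one arm is asked a week after the start and again at Week 4. The other is first asked at Week 4 about the whole four weeks. Mild, short-lived events in the first week are the kind most easily forgotten by then, so istradefylline could show more early events simply because it was asked sooner.

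Nothing in the article offsets this. The Limitations section offers the wearable device against open-label bias, but its listed outputs are movement, gait and sleep, not adverse events. Analysis cannot recover control-arm reports that were never collected. At stake is the by-arm reading of early adverse events, with the bias running against istradefylline.

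**Working it through.** **Counting contacts (Table 1 and footnotes a and c).**

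- Istradefylline, post-baseline safety contacts: Weeks 1, 4, 8, 12, 16, 20, 24, 28, 32, 36 and 37 = 11, of which 10 are mandated and Week 37 is optional.
- Control: the same list without Week 1 = 10, of which 9 are mandated and Week 37 is optional.
- First post-baseline contact: 1 × 7 = day 7 against 4 × 7 = day 28.
- Contacts within Weeks 1 to 4: 2 against 1.

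**Possible size.** The article gives no adverse-event rate and no recall rate, so these inputs are assumptions:

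- p = true risk of an event in the first four weeks, equal in both arms: 0.10 to 0.30.
- s = share of those events starting in the first week, with uniform onset: 7/28 = 0.25.
- First-week events are fully captured when asked at Week 1.
- q = probability that a first-week event is recalled when first asked at Week 4: 0.5 to 1.0.
- Events in Weeks 2 to 4 are captured equally in both arms at Week 4.

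Recorded risk on istradefylline = p. Recorded risk in control = p × [(1 − s) + s × q]. Hence the spurious difference = p × s × (1 − q), and the apparent risk ratio = 1 / [1 − s × (1 − q)].

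- q = 1.0, any p: difference 0, ratio 1.00.
- p = 0.10, q = 0.9: 0.10 × 0.25 × 0.1 = 0.25 points, ratio 1/0.975 = 1.03.
- p = 0.20, q = 0.7: 0.20 × 0.25 × 0.3 = 1.5 points, ratio 1/0.925 = 1.08.
- p = 0.30, q = 0.5: 0.30 × 0.25 × 0.5 = 3.75 points, ratio 1/0.875 = 1.14.

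The range is 0 to 3.75 percentage points. With 50 patients per arm, the upper end is 50 × 0.0375 = 1.9 patients.

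**Primary endpoint.** Table 1 schedules the first decision on a levodopa increase at Week 4 in both arms. The Week 1 contact therefore adds no opportunity for additional levodopa in either arm.

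**After the remedy.** With Week 1 in both arms, each has 11 post-baseline contacts, the first on day 7. Each still includes the optional Week 37.

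**The case against.** The strongest defence is that the Week 1 visit belongs to the regimen. The istradefylline dose step depends on tolerability, which cannot be judged without asking about adverse events, and control has no such step. This stands as a justification for the visit. It does not make collection equal, and nothing prevents control patients being asked the same questions.

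Second, the article does not say how events are elicited or whether they can be reported between visits. If reporting is continuous, or Week 4 recall is good, the bias shrinks to nothing. That is right, and it is why the range starts at zero.

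Third, no safety hypothesis is specified, and the bias counts against the drug, so it cannot make istradefylline look safer. This stands and limits the seriousness. Adverse events in a randomised trial will still be read side by side by arm.

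A reader might infer more from Week 37: that an investigator who knows the arm may skip the last safety contact, creating a second arm difference after a Week 36 levodopa increase. The documents do not support this. Footnote c applies to both arms and names neither a judge nor a criterion, and footnote e continues the wearable and diary for that week in patients who have not discontinued. An optional visit permits a difference between arms but does not create one.

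**Conclusion.** The point holds for Week 1. Unequal early collection is explicit in Table 1: day 7 against day 28, and 10 against 9 mandated contacts. Whether it distorts the results is unknown. It can raise recorded early events on istradefylline by 0 to about 4 percentage points in the first four weeks, on the assumed risks, uniform onset and recall set out above. Complete recall at Week 4 gives zero. The effect is modest, confined to early safety and without bearing on the primary endpoint. It would be wrong to say that control events are necessarily lost, since a first-week event can still be reported at Week 4.

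**What to change.** Add a short scripted telephone check of adverse events, hospitalisations and concomitant medication at Week 1 in the control arm, with the same wording as in the istradefylline arm. Leave the istradefylline Week 1 visit unchanged. The cost is about 111/2 ≈ 55 short calls and a small burden on sites.

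If accrual has passed, keep the full adverse-event table, add a sensitivity table restricted to events with onset after Week 4 in both arms, and state in the report that early contact was unequal. This costs one table and a sentence. The table shows whether an arm difference persists once contacts are matched; it does not repair the early comparison.

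Do not instead exclude events first reported at Week 1 and resolved before Week 4. Only istradefylline patients can lose events that way. For illustration, take 50 per arm, a 15% first-week risk of transient events, capture of 0.95 at Week 1 and recall of 0.60 to 0.80 at Week 4. Istradefylline would lose 50 × 0.15 × 0.95 = 7.1 patients with events, while control kept 50 × 0.15 × 0.60 = 4.5 to 50 × 0.15 × 0.80 = 6.0. That exceeds the excess being corrected (7.5 × 0.15 = 1.1 to 7.5 × 0.35 = 2.6 patients) and would hide early istradefylline events.

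For Week 37, at most collect the adverse-event item the same way in both arms by telephone.

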### Efficacy outcomes

The primary study endpoint is the comparison of the cumulative additional dose of levodopa-containing medications during the treatment period (from Week 0 to Week 37) between patients with PD who receive adjunctive istradefylline and those who do not.

Secondary efficacy endpoints are the between-group comparisons of additional levodopa doses on each observation day from Week 4 to Week 36; the number of days until the first dose increase after Week 4; change in dose of levodopa-containing medications until Week 36; CGI-S score and change in score; CGI-improvement scale (CGI-I) score (to measure the degree of improvement from the previous evaluation); patient global impression of severity (PGI-S) score and change in score; PGI-improvement (PGI-I) score (to measure the degree of improvement from the previous evaluation); mH&Y staging scale (ON/OFF) score and change in score; MDS-UPDRS part I score (nonmotor experiences of daily living), part II score (motor experiences of daily living), part III score (motor examination), part IV score (motor complications), and change in scores; Parkinson’s Disease Questionnaire-39 (PDQ-39) score and change in score; and correlations between any of the score changes. Correlations between CGI-S and other measures (e.g., MDS-UPDRS3, MDS-UPDRS4, and PGI-S) will be evaluated to confirm whether dose escalation decisions would differ between using CGI-S and using other measures.

Patients will also wear a wristband-type triaxial accelerometry system (UW-301BT, Hitachi Systems Ltd., Tokyo, Japan) on their non-dominant wrist for 7 days every 3 months during the study; data extracted from the wearable device will include movement frequency and intensity, gait (step count, pace, and laterality), and sleep (bedtime, awakening time, duration of sleep, sleep efficiency, sleep onset latency, movement during sleep, and number of episodes of getting out of bed).

Safety endpoints for this study will include adverse events and adverse drug reactions classified based on System Organ Class and Preferred Term defined in the Medical Dictionary for Regulatory Activities (Japan edition), using the most recent version at the time of coding.

Exploratory endpoints include evaluation of the correlation between the information extracted from the wearable device and the primary/secondary efficacy endpoints.

### Statistical methods

There have been no previous studies investigating the effect of istradefylline treatment on the flexibility of the doses of levodopa-containing formulations. Thus, we used real-world data based on information from the medical claims database (Medical Data Vision Co., Ltd., Tokyo, Japan) to estimate the between-group difference in the Mann–Whitney U test by simulating cumulative L-DOPA doses in PD patients (non-istradefylline treatment), which would ensure a power of 80% with groups of 50 patients. In this condition, an approximate 21.3% in between-group difference over a period of 9 months (270 days) is detectable as the area under the curve (AUC) of cumulative additional L-DOPA doses between treatments (data on file; Kyowa Kirin Co., Ltd., Tokyo, Japan). Based on the mean additional levodopa dose over 9 months (approximately 265 mg) in a previously published study [36], recommendation from the Expert Medical Advisory board for this study, and the clinical experience in Japan, we anticipated that istradefylline might suppress the dose increase of levodopa-containing medications by 20%. Therefore, the sample size was set at 111 patients, to allow for 10% drop-outs and to ensure that there were 50 patients per group with data evaluable for the efficacy analyses.

The efficacy and safety analysis sets will include all patients who meet the inclusion criteria and do not meet the exclusion criteria, with the exception of those who withdraw consent before the start of the observation period (Week 0) or are withdrawn by the study investigator, and those randomly assigned to istradefylline treatment but who do not start administration of istradefylline. The patient background data that will be collected will include date of birth (if not disclosed, age at the date of consent), sex, height, weight, caregiver availability, pregnancy, hospitalization, year of onset of PD, year of onset of wearing-off, family history of PD, year of initial treatment with levodopa, daily dose and number of administrations of levodopa, levodopa equivalent dose, MMSE score, and mH&Y (ON/OFF).

Summary statistics will be calculated for quantitative variables, and the number of patients and percentage will be determined for categorical variables. For the primary endpoint, the cumulative additional levodopa dose (AUC during the treatment period) will be calculated using the Mann–Whitney U test. The cumulative additional dose (AUC of additional dose during the treatment period) will be calculated as the total dose (daily dose × number of days) added to the dose of levodopa-containing medications (300–400 mg/day) at randomization. For the secondary endpoints, the cumulative additional doses of levodopa will be calculated for the patients who completed the treatment (Week 37). A log-rank test will be performed on the number of days from the start of observation (Week 0) to the time of dose increase, and time-to-event curves will be created using the Kaplan–Meier method. Summary statistics of the secondary endpoints at each observation time point will be calculated for each group, and mean and standard deviation data will be plotted in a line graph. Scores at each time point will be compared between groups using the Mann–Whitney U test. Correlation of the secondary endpoint scores will be performed using the Spearman correlation coefficient, and scatter plots will be created. A two-sided significance level of 5% will be applied to between-group comparisons, and two-sided 95% confidence intervals will be calculated. No imputation will be made for missing data. We will prepare a detailed statistical analysis plan before the database is finalized and locked. Statistical analyses will be conducted using SAS version 9.4 (SAS Institute Inc., Cary, NC, USA).

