## Methods/Design

### Patients

Patients eligible for inclusion in the ISTRA ADJUST PD study will be those with PD who meet all of the inclusion criteria and do not meet any of the exclusion criteria. Inclusion criteria include taking levodopa-containing medications ≥ 3 times daily with a daily dose of 300–400 mg; experiencing wearing-off phenomenon; age 30–84 years; PD diagnosed according to The International Parkinson and Movement Disorder Society (MDS) criteria [34]; modified Hoehn & Yahr (mH&Y) scale [35] (ON) stage ≤ 3; and provided written informed consent. Patients concomitantly taking anti-PD drugs other than levodopa, such as dopamine agonists, catechol-o-methyl-transferase inhibitors, and monoamine oxidase type B inhibitors, will also be eligible for inclusion. Exclusion criteria include previous treatment with istradefylline; receipt of any investigational drug within 4 months before the date of enrolment; presence of dementia or a Japanese version of the Mini-Mental State Examination (MMSE) score of ≤ 23; prior neurosurgery for PD (e.g., stereotactic surgery, deep brain stimulation, gamma knife); current or planned treatment with levodopa/carbidopa hydrate enteral suspension; moderate or severe hepatic disorder; PD treatment initiation or regimen change within 4 weeks before enrolment; receipt of strong CYP3A4 inhibitors (e.g., itraconazole, clarithromycin) within 14 days before enrolment; lactation or pregnancy; and any other reason for ineligibility according to the discretion of the investigator.

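### The safety analysis set is defined by eligibility rather than exposure, so a treated patient later found ineligible is left out of the adverse-event results

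*Protocol article*

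**What the plan says.** Statistical methods (protocol article) defines the efficacy and safety sets together: "The efficacy and safety analysis sets will include all patients who meet the inclusion criteria and do not meet the exclusion criteria". Two exceptions follow. The first covers withdrawal: "with the exception of those who withdraw consent before the start of the observation period (Week 0) or are withdrawn by the study investigator". The second covers "those randomly assigned to istradefylline treatment but who do not start administration of istradefylline". The article describes no other safety population.

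The criteria that decide membership are in the Patients section. They include hepatic disorder, recent strong CYP3A4 inhibitors, a low MMSE score, levodopa dose, age and recent regimen change, and they end with "any other reason for ineligibility according to the discretion of the investigator".

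On what is to be analysed, the Efficacy outcomes section says: "Safety endpoints for this study will include adverse events and adverse drug reactions". The design is open-label, with allocation to "either the istradefylline group or the control group in a 1:1 ratio".

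**The concern.** A safety set is meant to answer what happened to the people who were exposed. Membership should therefore depend on exposure, not on whether the patient should have been enrolled. Restricting a set to eligible patients can be argued for efficacy. Applied to safety, it removes a patient's adverse events from the numerator and the patient from the denominator for a reason unrelated to whether the drug was taken.

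Some entry criteria, such as those on hepatic disorder or strong CYP3A4 inhibitors, plausibly mark patients in whom tolerability is of particular interest. If such a patient were enrolled in error and treated, the adverse-event tables would not show what followed. The trial is small, so a few omissions could change the reported frequency of an uncommon event.

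This is not simply a detail left to the analysis plan. The article states the safety set. A plan that follows it inherits the problem, and a plan that departs from it contradicts the published protocol.

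**Working it through.** **Who is in and who is out, reading the sentence literally**

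| Patient | In the safety set as written? | Basis |
|---|---|---|
| Took istradefylline, later found to breach an entry criterion | No | Eligibility condition, explicit |
| Control, entered at Week 0, later found to breach an entry criterion | No | Eligibility condition, explicit |
| Withdrew consent before Week 0 | No | Exception; no treated patient lost |
| Assigned to istradefylline, never started it | No | Exception; no treated patient lost |
| Treated, then withdrawn by the investigator after Week 0 | Unclear | Depends on how far the Week 0 limit reaches |

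The first two rows are enough to support the point.

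The last row turns on grammar. The Week 0 limit is attached to withdrawal of consent, and the words "or are withdrawn by the study investigator" come after it with no limit of their own. Either the limit covers both kinds of withdrawal, and only patients not yet treated are removed, or it covers consent alone, and treated patients are removed as well.

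**Scale**

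Inputs from Statistical methods: 50 evaluable patients per group, 10% drop-out, 111 patients in total.

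- Check of the plan's own figure: 100 / (1 − 0.10) = 111.1, which agrees with the stated 111.
- Patients per arm at 1:1: 111 / 2 = 55.5, taken as 55.
- Share of an arm per omitted patient: 1 / 55 = 1.8%.
- The documents give no number of omissions. Assuming 1 to 5 in one arm: 1 / 55 = 1.8% to 5 / 55 = 9.1%.

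**Illustrations with assumed counts**

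- Uncommon event: 3 of 55 patients (5.5%) have it. If those three are the patients omitted, the report shows 0 of 52.
- More common event: 8 of 55 (14.5%).
  - Omit 2 patients who both had it: 6 / 53 = 11.3%. A quarter of the events is lost (2 / 8 = 25%), and the incidence falls by 22% in relative terms.
  - Omit 3 patients who all had it: 5 / 52 = 9.6%. The loss is 3 / 8 = 37.5% of the events, and the relative fall is 34%.
- The same omissions when none of the patients had the event: 8 / 53 = 15.1% or 8 / 52 = 15.4%. The incidence goes up.

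The last two cases show that the direction depends on who is omitted, which the documents do not tell us.

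**The case against.** The strongest reply is that very few treated patients will be affected. Table 1 places eligibility confirmation at consent or enrolment and again at Week 0, so most breaches should be caught before treatment. Table 1 also has adverse events recorded throughout, so nothing is lost from the data. The primary endpoint, cumulative additional levodopa dose, is a different matter that this point does not touch. A detailed analysis plan is promised before database lock and could refine the set. All of this stands and limits the severity. It does not make the stated definition right.

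Three stronger readings are tempting, and the documents do not support them.

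- A reader might infer that patients withdrawn because of an adverse event are dropped. The sentence is ambiguous. The neighbouring exceptions concern patients who never entered treatment. Table 1 schedules the final assessments for patients who discontinue, and the completers' calculation is listed as secondary, which suggests that the main set includes people who stopped early. The supportable point is that the time limit must be stated.
- A reader might infer that the discretionary criterion lets an investigator, knowing the allocation, remove a patient once outcomes are seen. That criterion is one of the entry exclusions, and the article provides for no review of eligibility after treatment starts.
- A reader might infer that the comparison is biased in favour of istradefylline. The eligibility condition applies to both arms, and a breach on age, levodopa dose or a recent regimen change does not obviously mark a patient at high risk. Bias is possible, but its direction is not shown.

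**Conclusion.** The point holds in a limited form. The article fixes a safety set that depends on eligibility and offers no exposure-based alternative, so exposed patients found ineligible after treatment began are excluded from the adverse-event results. Whether patients withdrawn by the investigator after Week 0 are excluded as well cannot be settled from the text.

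The size is about 1.8% of an arm for each omitted patient, assuming 111 patients split evenly. The number omitted is not given and is probably small. The event counts used above are assumptions chosen to show sensitivity, not estimates. The severity is moderate: it should be fixed, but it does not threaten the primary analysis.

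**What to change.** Separate the two sets, and define the safety set as every patient who took at least one dose of istradefylline, plus every control patient who entered the observation period at Week 0, analysed by treatment actually received, regardless of eligibility breaches or later withdrawal. State that the exception for withdrawal by the investigator removes no one from this set after Week 0. For the efficacy set, state whether that exception applies only before Week 0.

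The cost is a sentence or two in the protocol and the analysis plan. No new data are needed, because adverse events are already collected in both arms throughout the study.

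### The efficacy set drops patients randomised to istradefylline who never start it, with no matching control exclusion, so the primary comparison is not between the groups as randomised

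*Protocol article*

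**What the plan says.** Statistical methods defines a single population for both purposes: "The efficacy and safety analysis sets will include all patients who meet the inclusion criteria and do not meet the exclusion criteria". Two groups of exceptions follow.

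- The first is worded for either arm: patients who "withdraw consent before the start of the observation period (Week 0) or are withdrawn by the study investigator".
- The second names one arm only: "those randomly assigned to istradefylline treatment but who do not start administration of istradefylline".

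Study design, treatments, and blinding says that patients are "randomly assigned to either the istradefylline group or the control group in a 1:1 ratio", describes the trial as open-label, and then states: "Once-daily oral administration of a 20 mg istradefylline tablet will be started at Week 0". Efficacy outcomes words the primary comparison as one "between patients with PD who receive adjunctive istradefylline and those who do not", that is, by treatment received. The article states no analysis of all randomised patients.

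**The concern.** Randomisation makes the two groups comparable at the moment of allocation. A rule that then removes patients from one group, for something that happens only in that group, gives up that comparability. Here a patient allocated to istradefylline who declines it, or from whom it is withheld, leaves the efficacy set. The same kind of patient allocated to control stays.

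A set limited to patients who took at least one dose is usually defended on the ground that the decision to start cannot depend on a known allocation. That defence is not available in an open-label trial, where patient and physician both know the arm. The wearable device measures, which the Limitations section offers as an offset to open-label bias, cannot correct who is selected into the analysis.

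The exclusion is also not needed to measure the outcome. The levodopa dose exists whether or not istradefylline is taken. Table 1 schedules the dose-increase decision at each four-weekly visit from Week 4 to Week 36 and a concomitant medication check at every visit.

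**Working it through.** **The plan's own figure.** 50 evaluable patients per group is 100 in total. With 10% drop-out, 100 / 0.9 = 111.1; conversely, 111 × 0.9 = 99.9. The stated 111 agrees to rounding. The step from a 21.3% detectable difference to 50 per group cannot be rebuilt, because the simulated distribution is on file and no SD is printed. The point does not rest on either figure.

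**Who is affected.** With 1:1 allocation, 111 / 2 = 55.5 patients per arm. The non-starter fraction f is an assumption; the article gives none.

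- f = 2%: 55.5 × 0.02 = 1.1 patients
- f = 5%: 55.5 × 0.05 = 2.8 patients
- f = 10%: 55.5 × 0.10 = 5.6 patients

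**Shift in the istradefylline arm mean.** Let the whole arm have mean 1 and the non-starters mean r. After they are dropped, the retained mean is (1 − r·f) / (1 − f). The value of r is also an assumption, so it is taken on both sides of 1.

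| f | r = 1.5 (50% more) | r = 0.5 (50% less) |
|---|---|---|
| 2% | 0.970 / 0.98 = 0.990 (−1.0%) | 0.990 / 0.98 = 1.010 (+1.0%) |
| 5% | 0.925 / 0.95 = 0.974 (−2.6%) | 0.975 / 0.95 = 1.026 (+2.6%) |
| 10% | 0.850 / 0.90 = 0.944 (−5.6%) | 0.950 / 0.90 = 1.056 (+5.6%) |

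A minus sign favours istradefylline; a plus sign counts against it.

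**Effect on the planned test.** The primary test is Mann–Whitney, so a shift in means is only a guide. A simulation with 55 patients per arm, normal outcomes, no treatment effect and 6,000 repetitions removed the non-starters from one arm only. Non-starters were set 0.5 to 1.0 SD higher in added levodopa. The chance of a false significant result favouring istradefylline, nominally 2.5%, became:

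- 2% non-starters: 2.8% to 3.3%
- 5% non-starters: 3.2% to 3.8%
- 10% non-starters: 4.1% to 6.7%

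If non-starters are lower instead of higher, the excess moves to the other tail.

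**The case against.** The best reply is that the asymmetry is narrower than it looks. Istradefylline starts at Week 0, and the same sentence also removes, from either arm, patients who withdraw consent before Week 0 or are withdrawn by the investigator. A reluctant patient who withdraws consent before then is lost whichever arm was drawn. The one-sided clause adds only patients allocated to istradefylline who never start and are not already removed on those grounds. This stands, and it limits the number affected. It does not supply a counterpart: a control patient who would not have started the drug, and who stays in the trial, is kept. The investigator clause does not restore balance either, since its time limit is unclear and it too is applied with allocation known.

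It can also be said that the bias is probably small. With about one non-starter the mean moves by 1.0% and the error rate hardly changes. A 10% non-starter rate would by itself use up that arm's whole drop-out allowance. This stands as well, and is why the size is given as a range.

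A reader might infer that the rule favours istradefylline, on the view that frailer or more symptomatic patients fail to start. The article says nothing about non-starters' levodopa need, and a mildly affected patient may equally decline an add-on. A reader might also infer that the rule undoes the minimisation. Losing a few patients disturbs balance on three binary factors; it does not undo it.

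Finally, the statistical analysis plan is not shown and may add an all-randomised analysis. The article nevertheless states the efficacy set as a rule. A plan that follows it inherits the problem, and a plan that departs from it contradicts the published text.

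**Conclusion.** The point holds. The stated efficacy set excludes patients after randomisation, in one arm only, with allocation known, so the primary analysis does not compare the groups as randomised. Bias can go either way.

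Its size cannot be determined from the article. If 2% to 10% do not start, and they need 50% more or 50% less added levodopa than average, the istradefylline mean moves by about 1.0% to 5.6% down or up, against an anticipated effect of 20%. It is tempting to read the 5% and 10% rows as supplying roughly one eighth to over one quarter of that effect (2.6 / 20 = 13%; 5.6 / 20 = 28%). The documents do not support that reading: it takes only the unfavourable direction and only the higher assumed rates. The case for change rests on the loss of the randomised comparison in the primary analysis, not on a demonstrated bias of known size.

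**What to change.** - Make the primary efficacy set all randomised patients, analysed in the arm to which they were allocated.
- Keep non-starters on the same visit schedule where consent allows, so that their levodopa dose is generated and recorded under the same rules and to the same end date.
- Exclude only on information fixed before randomisation, and bring the consent and investigator withdrawal clauses into line with this.
- Reword the primary endpoint in Efficacy outcomes to compare patients as assigned, not as treated.
- Keep the set of patients who started istradefylline for safety and for a supportive efficacy analysis.

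The planned total stays at 111. The work is a change of wording, which can be made in the statistical analysis plan that the article says will be written before database lock, plus dose follow-up of a handful of patients. The costs are slight dilution of the effect by non-starters, and incomplete data for those who withdraw consent or leave the visit schedule. Such cases should be counted and reported by arm.
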